	**Medical data patient file**				
	Blood pressure	X	X	X	X
	Weight	X	X	X	X
To test the effectiveness of the MARS-intervention (experimental group) in promoting self-efficacy in comparison to CAU (control group).	**Questionnaires patient**				
	Self-efficacy (GSE)	X	X	X	X
To test the effectiveness of the MARS-intervention (experimental group) in promoting mental health in comparison to CAU (control group).	**Questionnaires patient**				
	Quality of life (WHOQoL-Bref)	X	X	X	X
	Depression & Anxiety (HADS)	X	X	X	X
	Positive & Negative affect (PANAS)	X	X	X	X
To test the effectiveness of the MARS-intervention (experimental group) in promoting social support in comparison to CAU (control group).	**Questionnaires patient**				
	Social support (MOS-SSS)	X	X	X	X
	(heiQ- subscale Social Integration and Support)	X	X	X	X
	(Self-developed item on who provides support in general and in relation to medication)	X	X	X	X

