**Secondary objectives important other from the social network**					
To test the effectiveness of the MARS-intervention (experimental group) in promoting mental health among an important other in the social network of the patient in comparison to CAU (control group).	**Questionnaires important other**				
	Quality of life (CarerQol-7D)		X	X	X
	Depression (PHQ-9)		X	X	X
	Anxiety (GAD-7)		X	X	X
	Positive & Negative affect (PANAS)		X	X	X
To test the effectiveness of the MARS-intervention (experimental group) in promoting social support among an important other in the social network of the patient in comparison to CAU (control group).	**Questionnaires important other**				
	Social support (MOS-SSS)		X	X	X
	(heiQ- subscale Social Integration and Support)		X	X	X
	(self-developed item on who provides support)		X	X	X

We hypothesized that medication adherence and self-management will be higher in the MARS-intervention (experimental) group than in the control group.

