### Randomization

Patients participating in the study are randomized after a run-in period, using block randomization at the patient level, at an 1:1 allocation ratio into either one of the two groups: control group or experimental group. Prior to the start of the study the randomization list was generated by a statistician (RT) using a macro [37] in SAS Enterprise Guide 7.13 (SAS Institute Inc., Vary, NC, USA) that automates the random assignment to treatment groups. To prevent predictability of the blocked randomization, block sizes were random and hidden to the researchers and therapists. Since age of the patient can be a confounding variable, in particular being above or below the age of 18 years, age was a stratification factor. Envelopes were numbered in the same order as the randomization list and the group allocation was put in the envelopes after which they were sealed, so that these could be taken to the home of the participant and revealed accordingly.

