### Procedure

Inclusion commenced in September 2018, but inclusion is recently stopped due to Covid-19. Data collection is still ongoing. Participants are being recruited from one academic hospital in the Netherlands where they received their kidney transplant or from the local hospital after referral for post-transplant care. Patients who are eligible for the study are informed about the study by the healthcare professional at the end of their regular appointment. Thereafter the healthcare professional or someone from the research team hands out written information on the study (PIF). The healthcare professional was provided with a standardized script on introducing the study. After having time to consider participation, the researcher contacts the patients by telephone to provide additional information (when needed), answer questions, ask for consent and make an appointment to obtain written consent. This appointment can take place at the patient’s home and the important other is also invited to attend. After written consent from both parties is obtained, the first questionnaires are completed (T0) and the electronic monitoring device is explained and handed out. Since evidence suggests that adherence will be statistically higher when patients start to use the electronic monitoring device [38], a run-in period of 35 days (+/− 7 days) is incorporated. A second appointment is made to coincide with the end of the run-in period (T1), during which a second set of questionnaires is completed by patient and important other, and EM data is collected. Group assignment is revealed after questionnaires have been completed. For the following 6 months patients allocated to the experimental group receive the intervention and the control group receives CAU. Six months after T1 participants are asked to complete questionnaires and EM data is collected (T2). Subsequently, patients continue using the EM device for the follow-up period of 6 months and questionnaires are also completed at the end of this 6 months (T3) (see Fig. 1 for flow-diagram) .

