#### Secondary study parameters

The proportions of adherent participants based on the CAS in both randomization groups will be analyzed with a chi-test with continuity correction. The influence of biological markers on adherence will be analyzed with a logistic regression.

The continuous secondary outcomes will be analyzed with linear multi-level regression analyses. The patients form the upper level, their measures at T1 and T2 the lower level. The covariance structure will be determined with the deviance score applying restricted maximum likelihood. Treatment group, T2, the group-T2 interaction and age will be postulated as fixed effects. In case of an abnormal distribution of the scores, an appropriate transformation (logarithmic, polynomial or Blom [73]) will be applied. If no satisfying transformation can be found, the outcome will be dichotomized on the median, and a multilevel logistic regression analysis will be performed. Binary outcomes will be analyzed with multilevel logistic regression analysis, using the same levels and fixed effects as described for linear multi-level regression analysis.

To analyze whether the intervention is sustainable 6 months after the treatment, a logistic multilevel analysis will be applied including the T1, T2 and T3 measures. Adherence will be the dependent variable, and treatment group, T2, T3 and group-time interactions will be the fixed effects. The group-T2 interaction effect will present the differential intervention effect, and the T2-T3-group contrast is the effect of interest for sustainability.

To answer the question when the intervention influences the adherence most, a multi-level logistic regression analysis will be applied. The EM devices can be read every 30 days, resulting in a baseline and 6 repeated measures (at 65, 95, 125, 155, 185 and 215 days). The fixed part of the model will include treatment group, the six follow-up time points and interactions.

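### The model for continuous secondary outcomes estimates a difference in change from T1 and leaves out T0, so it is valid but less precise than the collected baseline data allow

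*Protocol article*

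**What the plan says.** Protocol article, Statistical analysis, Secondary study parameters, gives the model for continuous secondary outcomes. On the occasions: "The patients form the upper level, their measures at T1 and T2 the lower level". On the fixed part: "Treatment group, T2, the group-T2 interaction and age will be postulated as fixed effects". T0 is neither an occasion nor a covariate there, and no other model in that section names it.

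Procedure describes two assessments before allocation is known. At the first visit "the first questionnaires are completed (T0) and the electronic monitoring device is explained and handed out". At the end of the 35-day run-in "a second set of questionnaires is completed by patient and important other, and EM data is collected". It then states: "Group assignment is revealed after questionnaires have been completed". Randomization agrees: "Patients participating in the study are randomized after a run-in period".

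Table 1 schedules T0, T1, T2 and T3 for the patient-level measures PiH-NL, GSE, WHOQoL-Bref, HADS, PANAS, MOS-SSS, heiQ, blood pressure, weight, IPV and eGFR. For the important other's scales it schedules T1, T2 and T3 only.

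**The concern.** Two features of the model cost precision.

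- **Free group effect at T1.** Randomisation makes the arms equal in expectation at T1, yet the model estimates a group difference there. With complete data the group-by-T2 term is then the difference between arms in mean change from T1. The age term does not alter this, because it enters as a main effect and does not adjust T2 for the T1 score. A change score subtracts the whole of a noisy baseline; baseline adjustment subtracts only the part that predicts T2.
- **T0 unused.** T0 and T1 both precede allocation, so both are legitimate baselines. A second reading can help to average out measurement error in the first.

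At stake is the width of the confidence intervals for the continuous secondary outcomes. The primary analysis is not affected.

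**Working it through.** **Figures in the plan.** The article states no SD, correlation or power for the continuous secondary outcomes, so there is no figure on this point to reproduce. The sample size supplies n only: Power calculation gives 81 per arm with 10% drop-out, and 81 × 0.9 = 72.9, about 73 evaluable per arm.

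**Assumptions.** Equal SDs on all occasions, complete data, and correlations r01 (T0-T1), r12 (T1-T2) and r02 (T0-T2). None of these is in the documents. Variances are in units of 2·SD²/n, so a comparison of T2 alone has the value 1.

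**Formulas.**
- Model as written (change from T1): 2(1 - r12)
- Adjusted for T1: 1 - r12². Relative to the model as written this is (1 + r12)/2, a cut of (1 - r12)/2.
- Adjusted for T0 and T1: 1 - (r12² + r02² - 2·r12·r02·r01)/(1 - r01²). With all correlations equal to r this is 1 - 2r²/(1 + r).

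**Equal correlations.**

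| r | As written | T1 adjusted | T0 and T1 adjusted | Cut from T1 adjustment | Further cut from T0 |
|---|---|---|---|---|---|
| 0.3 | 1.40 | 0.91 | 0.862 | 35% | 5% |
| 0.5 | 1.00 | 0.75 | 0.667 | 25% | 11% |
| 0.6 | 0.80 | 0.64 | 0.550 | 20% | 14% |
| 0.7 | 0.60 | 0.51 | 0.424 | 15% | 17% |
| 0.8 | 0.40 | 0.36 | 0.289 | 10% | 20% |

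A simulation at r = 0.6 with 73 per arm (8000 trials) gave standard errors of 0.148, 0.133 and 0.123 SD for the three analyses. The variance ratio of the last two is 0.851, against 0.55/0.64 = 0.859 by formula.

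**Unequal correlations.**
- Mild: r01 = 0.75, r12 = 0.70, r02 = 0.65. R² = (0.49 + 0.4225 - 0.6825)/0.4375 = 0.526, so the factor is 0.474. Against 0.51 for T1 alone, T0 adds about 7%.
- Faster decay: r01 = 0.7, r12 = 0.6, r02 = 0.5. R² = (0.36 + 0.25 - 0.42)/0.51 = 0.373, so the factor is 0.627. Against 0.64, T0 adds 2%. The same spacing of correlations with r12 from 0.3 to 0.8 gives 1-2%.
- T1 carries everything in T0 (r02 = r01·r12): T0 adds 0%.

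**In practical terms**, at r = 0.6 with 73 per arm, two-sided 5% and 80% power, the detectable difference is (1.96 + 0.84)·√(2v/73), where v is the variance factor:
- as written: 0.415 SD
- T1 adjusted: 0.371 SD
- T0 and T1 adjusted, equal correlations: 0.344 SD
- T0 and T1 adjusted, faster decay: 0.367 SD

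**The case against.** The strongest reply is that nothing here is wrong. The model gives a valid randomised comparison, the article promises no precision for these outcomes, and T1 is a reasoned reference: the run-in exists because adherence rises when the device is first used, and electronic monitoring has no T0. This stands as far as it goes. There is no bias, and a reader who inferred an invalid analysis would go beyond the documents. But the run-in does not justify discarding T0. A shift in means between T0 and T1 occurs before allocation in both arms and is absorbed by a time effect. Nor does it bear on the free group effect at T1.

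A second reply is that T0 may add little. The gaps are about 35 days (T0-T1), 180 (T1-T2) and 215 (T0-T2), so equal correlations are doubtful, and under decay the extra gain is 1-2% or nil. This stands. The internal consistencies quoted for the patient scales (roughly 0.66 to 0.91) suggest measurement error that a second reading would reduce, but they are not test-retest correlations and settle nothing.

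A third reply concerns scope. Blood pressure and weight come from electronic patient files, eGFR is also listed as patient-file data, and Control group says the interval between check-ups varies by patient. Separate T0 and T1 values are therefore not assured for these measures. This also stands.

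**Conclusion.** The point holds as a loss of precision. The more certain part is the change-score contrast: adjusting for T1 cuts the variance by (1 - r)/2 at any correlation below 1, which is 20% at r = 0.6 and 15% at r = 0.7. The part due to T0 is uncertain: 14-17% more under equal correlations at those values, about 7% in the mild unequal case, and 0-2% under fast decay or if T1 makes T0 redundant.

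A reader might add these up and infer that omitting T0 costs about 30% of the variance. Under equal correlations the total cut is indeed 31% at r = 0.6 (0.80 to 0.55) and 29% at r = 0.7 (0.60 to 0.424). But when T1 adjustment is taken first, it supplies 0.16 of the 0.25 reduction at r = 0.6 and 0.09 of the 0.176 at r = 0.7, so half or more of the total needs no T0. The documents give no correlation that would support the larger reading.

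The T0 gain does not apply to the important other's outcomes. For eGFR, blood pressure and weight it applies only where separate T0 and T1 readings exist.

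**What to change.** For patient outcomes, enter T0, T1 and T2 as occasions. Give T0 and T1 each their own time effect but no group effect (a common pre-randomisation mean), keep age, and use an unstructured covariance. The group effect at T2 is then baseline-adjusted, and a missing T0 or T1 score is handled by the likelihood.

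If T0 and T1 are entered as covariates for T2 instead, state how missing baselines will be imputed, because a standard mixed model drops records with a missing covariate.

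For the important other's outcomes, constrain the arms to a common mean at T1 or adjust for T1. For eGFR, blood pressure and weight, use T0 only where it is a reading distinct from T1.

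The cost is a sentence or two in the analysis section, with no new data and no burden on patients. The change should be recorded before outcomes are analysed by arm.

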**Secondary objectives patient**					
To test the effectiveness of the MARS-intervention in promoting the medication adherence as measured by secondary outcome measures in comparison to CAU (control group). To test whether the effectiveness of the MARS-intervention on medication adherence sustains after six months (T2-T3). To asses when the MARS-intervention influences medication adherence the most.	**Questionnaires patient**				
	Medication adherence (BAASIS)	X	X	X	X

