	**Medical data patient file**				
	Intra patient variability (IPV)	X	X	X	X
	Rejection of the graft (treatment for rejection)			X	X
	Graft loss			X	X
	Kidney functioning (eGFR)	X	X	X	X

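### The multilevel models for secondary outcomes stop at T2 although all these outcomes are collected at T3; the continuous adherence measures have no stated T3 model, and rejection and graft loss do not fit the T1/T2 model

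*Protocol article*

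**What the plan says.** Under Secondary study parameters, the model for continuous secondary outcomes is fixed in two sentences: "The patients form the upper level, their measures at T1 and T2 the lower level", and "Treatment group, T2, the group-T2 interaction and age will be postulated as fixed effects". Binary outcomes are to be analysed by multilevel logistic regression "using the same levels and fixed effects as described for linear multi-level regression analysis".

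A separate paragraph covers sustainability. There "a logistic multilevel analysis will be applied including the T1, T2 and T3 measures", and "Adherence will be the dependent variable, and treatment group, T2, T3 and group-time interactions will be the fixed effects". The effect of interest is the T2-T3-by-group contrast.

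The matching objective in Table 1 reads: "To test whether the effectiveness of the MARS-intervention on medication adherence sustains after six months (T2-T3)". The objectives for self-management, self-efficacy, mental health and social support, and those for the important other, ask for a comparison with care-as-usual and do not mention T2-T3.

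Table 1 marks every secondary measure at T3, and the Procedure section confirms that "questionnaires are also completed at the end of this 6 months (T3)". Rejection and graft loss are marked at T2 and T3 only.

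**The concern.** The protocol is not silent here. It names the time points and fixed effects, and they exclude T3. Followed as written, this has three consequences of different weight.

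- **Continuous adherence measures.** IPV and the BAASIS visual analogue scale bear on the objective of sustained medication adherence. The linear model stops at T2, and the model that reaches T3 is logistic.
- **Rejection and graft loss.** The binary model uses T1 and T2, but these outcomes are scheduled at T2 and T3.
- **All other scales.** Patients and important others supply T3 data that no stated between-group model uses. Which T3 contrasts to report is then left to be chosen after the results are known. Patients who miss T2 but attend T3 also contribute less than they could.

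**Working it through.** The protocol gives no figure to reproduce on this point. The check sets the schedule against the models and then sizes what is left out.

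**1. Schedule against stated model**

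| Outcome | Scheduled (Table 1) | Stated between-group model | T3 used? |
|---|---|---|---|
| BAASIS adherent/non-adherent category | T0-T3 | Can enter the logistic sustainability model | Possible |
| BAASIS visual analogue scale (0-100%) | T0-T3, as part of BAASIS | Linear, T1 and T2 | No |
| IPV | T0-T3 | Linear, T1 and T2 | No |
| Rejection, graft loss | T2, T3 | Logistic, T1 and T2 | No |
| eGFR, PiH-NL, blood pressure, weight, GSE, WHOQoL-BREF, HADS, PANAS, MOS-SSS, heiQ | T0-T3 | Linear, T1 and T2 | No |
| Important other: CarerQol, PHQ-9, GAD-7, PANAS, MOS-SSS, heiQ | T1-T3 | Linear, T1 and T2 | No |

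Counting IPV, there are 11 continuous patient measures and 6 important-other measures, 17 in all, plus the BAASIS visual analogue scale.

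**2. Is IPV an adherence measure?** Yes, by the protocol's own description. Under the Medication adherence heading of the secondary outcomes, medical-record data are said to give an impression of adherence, and IPV is the first example. Rejection, graft loss and eGFR follow as transplant outcomes. IPV therefore falls under the sustainability objective by definition. For eGFR the link rests only on the layout of Table 1.

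**3. Does the T1/T2 logistic model fit rejection and graft loss?** No T1 value is scheduled. With T2 rows only, the T2 indicator is constant and cannot be separated from the intercept, nor the group-T2 interaction from the group effect. If a T1 value were filled in for graft loss, it would be almost always no, because a functioning graft is required at inclusion and the run-in is 35 days. An interaction estimated against a time point with almost no events is not usable. Follow-up after randomization is six months to T2 and six more to T3, so stopping at T2 omits the second half.

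**4. What a T3 contrast could detect**

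Inputs: 81 per arm and 10% drop-out (Power calculation), so 81 × 0.90 = 72.9, about 73 evaluable. Two-sided 0.05, 80% power and the T1-T3 correlation r are assumptions; the protocol gives none of them for secondary outcomes.

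T1-adjusted contrast, in SD units: (1.96 + 0.84) × √(2/73) × √(1 − r²) = 0.463 × √(1 − r²)

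- r = 0.8: 0.463 × 0.600 = 0.28
- r = 0.7: 0.463 × 0.714 = 0.33
- r = 0.5: 0.463 × 0.866 = 0.40

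If the group-T3 interaction is read as a difference in change from T1, as happens when the group effect at T1 is left free, the last factor becomes √(2(1 − r)). This gives 0.29 (r = 0.8), 0.36 (r = 0.7) and 0.46 (r = 0.5).

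**The case against.** The strongest reply is that the sustainability objective is worded for medication adherence alone and has a matching model, supported by 180 days of electronic monitoring after T2. This stands. A reader might infer that the objective goes unanswered for every secondary outcome or every questionnaire. The documents do not support that: the BAASIS category can enter the logistic model, and no sustainability objective is stated for self-management, self-efficacy, mental health or social support. For those outcomes a T1/T2 model answers the end-of-treatment question that is asked.

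Second, a condensed article may leave T3 handling to a fuller document. This stands in part. The article does not say that T3 values will go unanalysed, so a reader who concludes that the trial can say nothing about lasting effects goes too far. But the article does state the time points of these models, and that statement can be judged.

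Third, two other analyses carry no time restriction: the logistic regression on biological markers and the test of the composite adherence score. Neither fills the gap. The first relates markers to adherence and does not compare a marker between groups. The second is a binary composite and does not use the visual analogue scale.

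Fourth, recruitment was stopped because of Covid-19, so 73 per arm may not be reached. This stands; with fewer patients the detectable differences are larger than those shown.

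**Conclusion.** The point holds in three parts. The clearest is the gap for IPV and the BAASIS visual analogue scale: adherence measures collected at T3, under an objective about T2-T3, with no stated model that handles them there. The second is a plain mismatch between the T1/T2 binary model and the T2/T3 schedule for rejection and graft loss. The third is weaker. eGFR and the remaining scales have T3 data outside any stated between-group model, but no stated objective is left unanswered.

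The primary analysis is not affected. The omitted comparisons would be informative: about 0.28 to 0.40 SD detectable with T1 adjustment, given 73 per arm and an assumed correlation of 0.8 to 0.5.

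**What to change.** - Extend the linear and logistic multilevel models for secondary outcomes to T1, T2 and T3, with fixed effects group, T2, T3, group-T2, group-T3 and age. The adherence model already has this time structure.
- Keep the T2 contrast as the main one. Label the T3 and T2-T3 contrasts as secondary.
- State that IPV and the BAASIS visual analogue scale are analysed for sustainability in the extended linear model, and name the adherence measure used in the logistic one.
- Take rejection and graft loss out of the multilevel model. Compare the groups on events after T1, through T2 and through T3.

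The cost is a few sentences and one more secondary contrast per outcome, which adds to the multiplicity among secondary results. No new data are needed. The Procedure section says that data collection was still under way, so the change could be fixed before the T3 results are examined.

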### Study population

#### Patients

The study population consists of kidney transplant recipients, aged 12 years and older, with no limitation to time since transplantation. Patients are required to have a subscription of IM and have a functioning graft at the time of inclusion. Graft functioning may be deteriorating, but as long as IM is required and the patient is not expected to be on dialysis within the next 3 months they can be included. In order to avoid convenience sampling multiple ways of assessing eligibility are being used. Kidney transplant recipients are eligible for inclusion when non-adherence is signaled by either themselves (self-report), or by the nephrologist or nurse practitioner (collateral report – professional) or someone in the patient’s social network (collateral report- social network). These three indicators combined form a composite adherence score (CAS). An affirmative answer on one (or more) of these indicators is sufficient to invite the recipient to participate. A CAS is more sensitive than using a single measure of non-adherence [31, 34–36]. Furthermore, non-adherent patients who do not explicitly acknowledge their non-adherence as a problem can be identified using the CAS. Professionals form an impression of adherence through, for example, conversations with the patient, clinic attendance and blood assay monitoring. Potential participants who meet any of the following criteria will be excluded from participation: 1) patients classified as adherent on all three of the indicators forming the CAS, 2) patients on dialysis or who are expected to start dialysis within the next 3 months, 3) patients who do not understand the Dutch language, 4) patients prior to their first transplant, and 5) patients with severe psychopathology or ongoing psychological treatment. In contrast with most other studies, patients with cognitive limitations (incapacitated) are not excluded from participation because their representative(s) and social network can be involved in the intervention and give complementary information regarding problems the patient is facing.

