##### Self-management

The 12-item Partners in Health Scale (PiH_NL) [50] is used to evaluate patients’ self-management skills. Patients can answer on a 8-point Likert scale. The PiH-NL consists out of two subscales: 1) knowledge and coping; 2)recognition plus management of symptoms, and adherence to treatment. The Cronbach’s alphas of the subscales were .80 and .72 referring to a good and acceptable internal consistency respectively. The correlation between the subscales was .43 [50].

Blood pressure and body weight are being used as clinical endpoints and are obtained from electronic patient files.

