### Statistical analysis

#### Power calculation

To our knowledge there was no (multi) systemic intervention study carried out among kidney transplant recipients at the time this project commenced, making it difficult to conduct a power analysis based on a comparable study. Therefore, the power calculation is based upon a behavioral intervention study among a group of heart, liver and lung transplanted patients [72]. The intervention group showed an adherence proportion of 95.1% and the control group a proportion of 79.1%. As the MARS-intervention is more intensive than the intervention of Dobbels et al. [72] we will perform an interim analysis when half of the participants have been included. We applied a 2-sided alpha of 0.029 and a power of 0.80. Anticipating a drop-out of 10%, this led to a target of 81 participants in both groups, a total of 162.

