## Discussion

Kidney transplantation is considered the best treatment for End Stage Renal Disease. However, medium- and long-term results are being undermined because of non-adherence to the IM regimen and inadequate self-management [1]. Optimizing adherence and self-management among kidney transplant recipients has been a topic of research for several decades, but effective interventions remain scarce [20, 72]. Accordingly, our aim was to test the effectiveness of a newly developed intervention for promoting medication adherence and self-management among kidney transplant recipients; the MARS-intervention. With the present study we took into consideration shortcomings described in the literature resulting in several strengths of the current RCT. First, the MARS-intervention addresses limitations of previous interventions. It is an outreaching, (multi) systemic, theory-driven and tailored intervention. Second, chances of including a convenience sample are minimized due to the way in which patients are assessed for eligibility and the outreaching nature. Third, the current study aims to include both adolescent as well as adult participants in contrast to most other studies that focus on one or the other. Although non-adherence among adults is common, adolescence has been recognized as a period in which non-adherence is highly prevalent [14, 74] and behavior established during adolescence is predictive for behavior during adulthood [75]. Moreover, transition from pediatric to adult care has been highlighted as a risky period when it comes to adherence [76–79]. Fourth, the current study takes the social network into account, not only when it comes to participation in the intervention but also when assessing the effect of the intervention. A fifth strength of the study is the use of multiple measures of adherence. The gold standard, EM, is the primary outcome. Nevertheless, adherence is assessed in different ways as a secondary outcome allowing triangulation, which enhances reliability [12]. Furthermore, not only measures for assessing adherence are taken into account, but transplant outcomes are assessed as well. Despite the best intentions when designing this study, there are some limitations of the study. In the current study only transplanted patients were eligible for inclusion. This is mainly due to practical reasons, for example to avoid differences in measurements for assessing adherence. However, pretransplant patients are an important group, since some transplants are postponed because of non-adherence to the pretransplant regimen. Furthermore, in the current protocol the nephrologist or NP is blinded. Although this has the advantage of preventing a bias in the care-as-usual from nephrologist or NP, it also has the disadvantage of not being able to confer with the nephrologist/NP or involve them in the sessions with the patient. As the healthcare professional is an important figure in the ecological environment of the patient, it would be beneficial to involve them and their participation could be integrated into the protocol if this intervention proves to be effective. In conclusion, there is a need to improve adherence and self-management among kidney transplant recipients to optimize clinical outcomes as well as patient wellbeing. If the MARS-intervention proves to be effective, it will be a useful tool to support non-adherent transplant recipients in changing their behavior with support of the social network.

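### For body weight, the T1-T2 model adjusts for age only as a main effect, so adolescent growth stays in the residual and the group-by-T2 test is somewhat conservative

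*Protocol article*

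**What the plan says.** Under Secondary study parameters the Protocol article fixes one approach: "The continuous secondary outcomes will be analyzed with linear multi-level regression analyses". It sets the structure, "The patients form the upper level, their measures at T1 and T2 the lower level", and names the fixed part: "Treatment group, T2, the group-T2 interaction and age will be postulated as fixed effects". The only interaction listed is group by T2.

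Body weight falls under this model. Table 1 schedules it at T1 and T2, and the Self-management section says: "Blood pressure and body weight are being used as clinical endpoints and are obtained from electronic patient files".

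The age range is wide: "The study population consists of kidney transplant recipients, aged 12 years and older". The Discussion counts this as a strength, noting that "the current study aims to include both adolescent as well as adult participants". The Randomization section gives the reason for stratifying on age: "in particular being above or below the age of 18 years, age was a stratification factor".

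The article gives no expected share of minors and no figures for weight change.

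**The concern.** T1 and T2 lie six months apart. Over that time growing adolescents can be expected to gain weight in a way that adults do not. The age term looks as if it deals with this, but it adjusts the level of weight and not its change, and the treatment effect is estimated from the change.

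The design balances the arms on the under-18 / 18-and-over split. The model of change takes no account of that balance, so growth differences between strata are counted as noise. What is at stake is some power on one secondary outcome.

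**Working it through.** **Why the age term drops out.** With two visits and complete data, the group-by-T2 coefficient is the difference between arms in mean T1-to-T2 change. A term β × age is the same at T1 and T2, so it subtracts out of each patient's change.

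**Inputs from the protocol.** 162 randomised 1:1, with 10% drop-out ("Anticipating a drop-out of 10%, this led to a target of 81 participants in both groups, a total of 162"), leaves 162 × 0.9 = 145.8, about 146 completers. The 81 per arm belongs to the primary outcome. The arcsine formula with 95.1% v 79.1%, two-sided alpha 0.029 and power 0.80 gives 72.3 per arm, and 72.3 / 0.9 = 80.3, rounded up to 81. Nothing below depends on that derivation. The protocol has no figure for weight to reproduce.

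**Assumed inputs (not in the protocol).** Share of minors p = 5-30%; extra six-month growth in minors d = 1.5-3.5 kg; within-stratum SD of change s = 3-4 kg; two-sided 5% test; a treatment effect giving about 80% power when the stratum-by-T2 term is in the model.

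**Formulas.**
- Standard error with stratum-by-T2 in the model: SE = 2s/√146. For s = 3 this is 0.497 kg.
- Leaving the term out multiplies the model's standard error by f = √(1 + p(1−p)d²/s²).
- Stratified allocation keeps the true sampling SD near the smaller value. Approximate type I error is therefore 2[1 − Φ(1.96 f)], and approximate power is Φ(1.96 + 0.842 − 1.96 f).

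**Worked case, p = 0.20, d = 2.5, s = 3.** p(1−p)d²/s² = 0.16 × 6.25/9 = 0.111, so f = 1.054. The planned standard error is 0.497 × 1.054 = 0.523. Type I error is 2[1 − Φ(2.066)] = 3.9%. Power is Φ(0.736) = 76.9%, a loss of 3.1 points.

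**Simulation.** 20,000 trials per case, randomised within age stratum in random blocks of 2, 4 or 6 (block sizes assumed), each patient then lost with probability 10%.

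| Minors | d (kg) | s (kg) | f | Type I, formula | Type I, simulated | Power loss, formula | Power loss, simulated |
|---|---|---|---|---|---|---|---|
| 5% | 1.5 | 4 | 1.003 | 4.9% | 4.9% | 0.2 | 0.2 |
| 10% | 2.5 | 3 | 1.031 | 4.3% | about 4.1-4.6% | 1.7 | about 1.5-2 |
| 10% | 3.5 | 3 | 1.060 | 3.8% | about 4.1% | 3.4 | about 3.6 |
| 20% | 2.5 | 3 | 1.054 | 3.9% | about 4.1% | 3.1 | about 3 |
| 20% | 3.5 | 3 | 1.104 | 3.1% | about 3% | 6.2 | about 6.6 |

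The formula assumes perfect balance. Incomplete blocks and drop-out leave a little imbalance, so the true SD is slightly above 0.497 (simulated 0.501 at p = 0.20, d = 2.5, s = 3, against a planned mean standard error of 0.523). In the extreme case of 30% minors and 3.5 kg, simulated type I error is 3.0% and power falls from 79.2% to 70.8%.

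With stratum-by-T2 added, type I error was 4.9-5.2% in the cases run for both models. Bias in the planned estimate was below 0.01 kg.

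**Where the conservatism comes from.** Under simple instead of stratified randomisation, the planned test has type I error 4.9% (20% minors, 2.5 kg, s = 3) and 4.7% (30%, 3.5 kg). The cause is the combination of stratified allocation with a model of change that omits the stratum.

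**Would linear age-by-T2 do?** Mean standard errors for planned / linear age-by-T2 / stratum-by-T2, with ages assumed uniform on 12-18 and 18-75, give the share of lost precision recovered:
- 10%, 2.5 kg, s = 4: 0.674 / 0.672 / 0.662, so 0.002/0.012 = 17%
- 10%, 2.5 kg, s = 3: 0.511 / 0.508 / 0.496, so 0.003/0.015 = 20%
- 20%, 2.5 kg, s = 4: 0.683 / 0.676 / 0.662, so 0.007/0.021 = 33%
- 20%, 2.5 kg, s = 3: 0.523 / 0.513 / 0.496, so 0.010/0.027 = 37%
- 30%, 3.5 kg, s = 3: 0.564 / 0.531 / 0.497, so 0.033/0.067 = 49%

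**The case against.** The strongest reply is that nothing here is wrong: the test is valid, the estimate is unbiased, age is already in the model, and special handling of one outcome in growing minors belongs in an analysis plan. The first three parts are true, and they hold this to a minor point. The last does not dispose of it, because the article does not leave the model open. It lists the fixed effects by name for all continuous secondary outcomes, and the trial already randomises by the factor that is missing from the change.

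A second reply is that the share of minors, the growth difference, the SD and the 80% benchmark are all assumed, and that the protocol claims no power for weight. That also stands. The documents establish the mechanism and its direction; the size can only be shown as a range. Recruitment had also stopped because of Covid-19, so 162 may not be reached.

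A reader might infer that uneven growth biases the weight comparison or raises the risk of a false positive. The documents do not support that: stratification at 18 balances growth between the arms, and the error runs towards caution. Nor does the point reach the main result, since electronically monitored adherence is compared with a continuity-corrected chi-square test that does not use this model.

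**Conclusion.** The point holds as a minor loss of efficiency on one secondary outcome. The planned weight test is unbiased but conservative whenever minors enrol and grow faster than adults.

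It is negligible with about 5% minors and 1.5 kg extra growth. At 10% minors it is small only if extra growth is at most 2.5 kg; at 3.5 kg and an SD of 3 kg about 3.6 power points are lost. It would therefore be too reassuring to call it negligible at any share up to 10%. At 20% minors the loss is about 3 to 6.6 points as extra growth goes from 2.5 to 3.5 kg, again with an SD of 3 kg. A larger SD shrinks all of these.

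**What to change.** For body weight, add the age stratum (<18 / ≥18) and its interaction with T2 to the fixed effects. Use the stratum and not linear age-by-T2 alone, which recovers only about 17-49% of the lost precision in the settings checked.

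The cost is one sentence and two extra parameters, on a factor already recorded for randomisation. If few minors enrol, the growth term will be imprecise and the gain close to nil.
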